#### Screening for perinatal infection

Preclinical evidence suggests that co-existent bacterial infections, particularly those due to gram-negative bacteria, may negate the neuroprotective effects of hypothermia. Therefore, we will perform advanced molecular, histological and transcriptomic evaluation in addition to standard automated blood cultures (Bactec), to identify any co-existent perinatal infection (Fig. 1). Whenever possible, bloods will be collected before giving antibiotics. Babies who had antibiotics before the blood collection (for example, babies referred from other hospitals) will be noted separately.

**Fig. 1 Fig1:**
[figure not shown]
Schedule of enrolment, intervention, and assessments

This will include:blood for targeted polymerase chain reaction (qPCR) to transcriptomic signatures to detect common bacterial pathogens within 6 h of birth;a small section of the umbilical cord (fetal end) for histopathological examination for funisitis. In addition, a section from the placenta will be collected whenever feasible. An experienced perinatal pathologist will report histopathology, masked to the clinical data.

We will use multiplex real time PCR (qPCR) on blood to identify babies with neonatal sepsis, using a panel of primers for both specific detection of common pathogens and generic detection. This will include *Enterobacteriacae*, *Fusobacteria* spps., *Staphylococcus aureus*, coagulase-negative *Staphylococci*, and *Streptococcus* spps including Group A and B *Streptococcus*, *Pneumococcus* and *Peptostreptococcus* spps), qPCR for quantitation of total 16 s rDNA [26]. Our preliminary data suggest the vast majority of pathogens are gram-negative, and unlike in high-income countries, group B streptococci is extremely rare in these settings.

Following RNA extraction from the whole blood collected in an RNA stabilising solution, we will perform next generation sequencing (paired end) and alignment. The sequenced data will be examined for the established signatures of bacterial infections recently reported from Imperial College London [27].

#### Magnetic resonance imaging and spectroscopy

The treatment effect of cooling therapy on brain injury will be assessed and quantified using MRI and spectroscopy. All recruited infants (surviving beyond 1 week) will have an MR scan at 7–14 days of age. Preparation of the baby for MRI is given in Additional file 2.

All MR scans will be performed on 3 T scanners (Philips, Siemens or GE) using common harmonised sequences developed as a part of the Magnetic Resonance Biomarkers in Neonatal Encephalopathy (MARBLE) study﻿﻿ [28]. 3 T MR scanning offers considerable benefits for MR spectroscopy, over 1.5 T imaging.

MR scanners will be calibrated using adult volunteer brain scans using the same sequences.

#### Conventional MRI protocol

T1-weighted – 3D MPRAGE (1-mm isotropic resolution);T2-weighted – 2D axial TSE (0.5-mm in-plane resolution, 3-mm slices);Diffusion – 2D axial SE-EPI (2-mm isotropic resolution, b = 0.750 s mm^-2^).

#### MR spectroscopy protocol

Surveys pre- and post-spectroscopy for detection of gross motion;PRESS (15 × 15 × 15 mm^3^, water suppressed, echo time = 288 ms) for metabolite peak area ratios;STEAM (15 × 15 × 15 mm^3^, water suppressed, dual repetition time, echo time = 20 ms) for relaxation corrected metabolite signals;STEAM (15 × 15 × 15 mm^3^, water unsuppressed, fixed repetition time, multiple echo times) for internal water referencing to provide metabolite concentrations.

The anonymised MR data will be encrypted and transferred to the Centre for Perinatal Neuroscience by Imperial College London file transfer protocols for analysis and storage. All MR data will be analysed centrally, masked to the allocation or other outcomes. Details of MR sequences are given in Additional file 3.

The raw spectroscopy data will be post-processed using software developed in-house at Imperial College London (Python v2.7) and an in-house implementation of TARQUIN will be used to calculate metabolite concentrations from the STEAM spectra. LCModel will be used to calculate metabolite peak area ratios from the PRESS spectra.

Diffusion imaging data will be processed using the FMRIB Software Library (FSL, v5.0) and registered across individuals using DTI-TK (http://dti-tk.sourceforge.net/pmwiki/pmwiki.php). The resulting maps of diffusion tensor indices will be compared between participants using FSL. Postnatal age and postmenstrual age at scan will be introduced as confounding variables into the general linear model rendering results age-independent.

#### MR biomarker endpoints

thalamic N-acetylaspartate concentration determined from STEAM spectroscopy;thalamic lactate/N-acetylaspartate metabolite peak area ratio determined from PRESS spectroscopy;white matter fractional anisotropy determined from diffusion imaging using tract based spatial statistics;brain injury severity score determined from conventional MRI [20].

### Follow-up and neurological assessments

The recruiting centres will maintain regular (3–6 months) telephone contact with parents to minimise attrition. The following information will be recorded at each contact:general health status of the baby;any change in home address or telephone number.

Each recruiting centre will have a dedicated and experienced neurodevelopmental paediatrician trained in Bayley Scales of Infant Development (Version III), who will assess the babies aged 18–22 months, masked to the allocation. Inter-observer variability will be addressed and corrected before the start of assessments, by comparing against a gold standard examiner (RS; Pearson’s trainer for Bayley Scales of Infant Development (Version III). The Bayley scales will be administered in one of the local languages (mother tongue of the child) – Hindi, Marathi, Kannada, Tamil, Malayalam, Singhalese, Telugu or Bangla.

Detailed medical history, neurological examination and Gross Motor Function Classification System assessment will be also obtained during this visit using a pre-defined proforma and then entered into the HELIX trial database.

Severe disability will be defined as any one of the following: Bayley III cognitive composite score < 70; Gross Motor Function Classification System level 3–5; hearing impairment requiring hearing aids/cochlear implant; or blindness.

Moderate disability will be defined as cognitive composite score 70–84 and one or more of the following: Gross Motor Function Classification System level II; hearing impairment with no amplification/cochlear implant; or a persistent seizure disorder.

The examiner will feed back the results of the neurodevelopmental outcome tests to the parents, immediately after the assessment. A copy of this report will be provided to the local principal investigator for clinical management. We will also collect information of various morbidities and medical support required during infancy and obtain detailed anthropometry to assess the nutritional status during the 18-month follow-up visit.

### Adverse events

All known adverse events relating to neonatal encephalopathy and cooling therapy are described in the parent information leaflet and will be part of obtaining the informed research consent, before the start of cooling therapy.

The following clinical events (1–9) occur due to the underlying disease (neonatal encephalopathy). Cooling trials from high-income countries have shown that cooling therapy reduces/does not increase the incidence of many of these clinical events in encephalopathic babies.Death during neonatal period or during infancyBrain injury observed with MRIAdverse neurodevelopmental outcome at 18 months and at childhoodPersistent pulmonary hypertensionMetabolic imbalancesCardiac arrhythmiaRenal failureCoagulopathyGastric bleeds

Cooling therapy may increase the risk of the following adverse events noted in the previous randomised controlled trials.Thrombocytopenia and increased need for platelet transfusionsSubcutaneous fat necrosis

All adverse events are expected to occur within the cooling period (first 72 h) or within 72 h of re-warming. Adverse reactions occurring subsequently (after one week of life), except subcutaneous fat necrosis, will not be considered as intervention related. Subcutaneous fat necrosis may occur several weeks after the therapy.

If an unexpected serious adverse event (SAE) occurs (i.e. an event not mentioned in the above list), it should be reported to the HELIX trial manager within 24 h, using one of the SAE report forms. The HELIX trial manager will ensure that the independent data monitoring committee (IDMC) and the research ethics committee (REC) are informed accordingly.

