## Background

Every year, approximately one million babies die in low- and middle-income countries (LMIC) due to neonatal encephalopathy – a condition arising from an unexpected lack of cerebral blood flow and oxygen supply to the fetal brain at the time of birth [1]. Approximately one-third of infants with moderate or severe encephalopathy will die during the newborn period and up to three-quarters of survivors will develop long-term neurodisability [2, 3]. Until recently, there was no effective treatment for this condition and the management was limited to supportive care.

Several high-quality cooling trials have been conducted in high-income countries in the past decade [4–6]. The meta-analyses of these trials have convincingly demonstrated that selective head or whole-body cooling, along with optimal tertiary intensive care, reduces mortality (risk ratio [RR] 0.8; 95% confidence interval [CI] 0.7–0.9; *p* = 0.005) and improves survival with normal neurological outcome (RR 1.5; 95% CI 1.2–1.9; *p* < 0.001) after neonatal encephalopathy in these settings [7, 8]. The protective effect of cooling persists into later childhood [9, 10]. Whole-body cooling is now widely used as a standard therapy for encephalopathy in the UK and other high-income countries [11].

The safety and efficacy data on cooling therapy from high-income cooling trials cannot be extrapolated to LMICs, due to differences in population co-morbidities, particularly co-existent perinatal infection, growth restriction and meconium aspiration syndrome, and lack advanced cardio-respiratory intensive care facilities [12]. Preclinical data suggest that the brain injury is worse and the neuroprotective effect of hypothermia in neonatal encephalopathy is lost in the presence of co-existent infection, particularly with gram-negative organisms [13].

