We systematically reviewed the published literature on the safety and efficacy of cooling therapy for neonatal encephalopathy due to hypoxia-ischemia in LMICs [14]. All published studies were small and/or of poor quality. Two studies reported increased mortality with cooling [15, 16]. A meta-analysis of all these trials showed a trend towards reduced mortality; however, this was not statistically significant (RR 0.74; 95% CI 0.4–1.3). More importantly, the CIs were wide and therefore significant benefits or harm could not be excluded. There were no data on long-term neurological follow-up after cooling therapy [14]. Thus, before cooling therapy is widely used as standard care therapy in LMICs, safety and efficacy data from adequately powered clinical trials are required.

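### The adverse-event section settles causality in advance, by a list of nine events and a one-week cut-off, against the protocol's own Background; the effect is confined to relatedness labels and the 24 h report

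*Protocol article*

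**What the plan says.** All three rules stand in the Adverse events section of the protocol article.

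- **Attribution by list.** "The following clinical events (1–9) occur due to the underlying disease (neonatal encephalopathy"). Nine events follow, beginning with death in the neonatal period or infancy. The support offered is this: "Cooling trials from high-income countries have shown that cooling therapy reduces/does not increase the incidence of many of these clinical events in encephalopathic babies".
- **Attribution by time.** The section first gives a window: "All adverse events are expected to occur within the cooling period (first 72 h) or within 72 h of re-warming". It then turns the window into a rule: "Adverse reactions occurring subsequently (after one week of life), except subcutaneous fat necrosis, will not be considered as intervention related".
- **Expedited reporting.** "If an unexpected serious adverse event (SAE) occurs (i.e. an event not mentioned in the above list), it should be reported" to the trial manager within 24 h, who informs the IDMC and the ethics committee.

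The Background takes a different position on the same evidence: "The safety and efficacy data on cooling therapy from high-income cooling trials cannot be extrapolated to LMICs". On studies in low- and middle-income countries it says: "Two studies reported increased mortality with cooling". It gives a pooled mortality risk ratio of 0.74 (95% CI 0.4 to 1.3) and concludes that "the CIs were wide and therefore significant benefits or harm could not be excluded".

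**The concern.** Whether cooling adds deaths, bleeding, arrhythmia or other complications in these hospitals is one of the trial's own questions. A rule that assigns such events to the disease, or to nothing connected with cooling once a week has passed, answers it beforehand at the level of the single case. The evidence used is the kind that the Background says cannot be carried over, and it is claimed for many of the events only, not for all nine.

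At stake is how the safety record reads. Under the rule as written, a reaction in a cooled baby on day 8 or at 6 months could be recorded as an event but not as related to cooling, whatever the investigator thought. A death in the cooled arm is a listed event, so it does not trigger the 24 h report.

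**Working it through.** No sample-size or power figure is involved. The check compares the sections and tests the window.

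**1. The list.** Death; brain injury on MRI; adverse neurodevelopmental outcome; persistent pulmonary hypertension; metabolic imbalances; cardiac arrhythmia; renal failure; coagulopathy; gastric bleeds. That is 9, as the section numbers them.

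**2. The window.** Age at the end of the stated window = age at start + cooling + re-warming + 72 h.

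- Start: 0 to 6 h (Inclusion criteria). Cooling: 72 h at 33.5 °C, then re-warming at 0.5 °C per hour (Abstract, Cooling therapy).
- The end temperature for the cooled arm is not given. I assume 36.5 to 37.0 °C, so re-warming takes (36.5 − 33.5)/0.5 = 6 h to (37.0 − 33.5)/0.5 = 7 h.
- Shortest: 0 + 72 + 6 + 72 = 150 h (6.25 days). Longest: 6 + 72 + 7 + 72 = 157 h (6.54 days).

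One week is 168 h, so the cut-off clears the window by 11 to 18 h. As a statement of when events are expected, it is arithmetically sound. The fault lies in using an expectation as a rule on causality.

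**3. The list against the window.** The section expects all adverse events within 72 h of re-warming. Yet it lists death in infancy and neurodevelopmental outcome at 18 months and in childhood, which arise or are assessed far outside that window.

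**4. What depends on the label.** The 24 h report turns on two conditions: the event is serious, and it is not listed. Neither relatedness nor age enters. The main analysis is by intention to treat (Statistical methods). Nothing in the article uses the relatedness label to select events for analysis or for the IDMC.

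**5. What is compared by arm anyway.**

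| Event | Between-arm comparison named in Outcome measures or Aims |
|---|---|
| Death | In the primary composite; also before discharge and at 18–22 months |
| MRI injury, neurodevelopment | MR biomarkers; disability at 18–22 months |
| Pulmonary hypertension, arrhythmia, renal failure, coagulopathy, gastric bleeds | Yes, before discharge |
| Metabolic imbalances | Persistent acidosis only, before discharge |
| Necrotising enterocolitis, pneumonia (unlisted) | Yes, before discharge, with no one-week limit |
| Sepsis (unlisted) | Early-onset, culture-proven only |
| Non-fatal events after discharge | Disability and microcephaly only |

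Morbidities during infancy are collected at the 18-month visit (Follow-up and neurological assessments). The article names no comparison for them. The analysis plan may do so, so I do not count this as an omission. It does show where the label carries most weight.

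**The case against.** The best defence is that the list of nine works as an expectedness list. Its only operative use is to define which serious events are unexpected. Where about one-third of such infants die in the newborn period (Background), a single death cannot be attributed individually, and comparison by arm is the informative method. Exempting such events from case-by-case reporting is a common choice. The IDMC reviews data by masked arm every six months or 50 babies, its Chair may arrange meetings as needed, and it may report a safety signal whatever the attributed cause.

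Most of this stands. It does not rescue the wording. An expectedness list says that events are common in this population; this one says what causes them. Nor does it explain the one-week rule, which expedited reporting does not need.

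Three stronger readings are tempting and are not supported:

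- **Late serious infection or bowel disease would escape notice.** Neither is on the list, so a serious case at any age goes by the 24 h route. The same holds for serious intracranial or pulmonary haemorrhage.
- **An excess of deaths could not be seen.** Death is compared by arm at discharge and at 18–22 months, and the IDMC sees masked data at each review.
- **The deaths between reviews measure the harm.** With steady accrual, 408/36 = 11.3 babies per month, so 50 babies take 50/11.3 = 4.4 months, and one-third of 50 is about 17 deaths. That is an expected total over both arms, with no excess, and it would occur under any reporting rule. It describes the spacing of reviews, which nothing here shows to be too wide.

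**Conclusion.** The point holds in limited form. The Adverse events section attributes nine events, including death, to the disease, and rules out relatedness after one week with a single exception, subcutaneous fat necrosis. Both conflict with the Background, and the list does not fit the section's own window.

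The consequences are two: individual relatedness labels may be wrong for reactions from one week of age up to follow-up at 18–22 months, and listed events do not trigger the 24 h report. The primary comparison, its error rates and the sample size are untouched. The practical weight falls on late non-fatal events, where disability and microcephaly are the only named comparisons after discharge.

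This rests on the article alone. The full protocol's safety section, the analysis plan and the IDMC's reporting format are not shown and may already provide the tabulation proposed below. The window check assumes re-warming to 36.5–37.0 °C, but the conclusion does not depend on it.

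**What to change.** 1. Delete the sentence that rules out relatedness after one week.
2. Reword the introduction to the nine events so that it calls them expected in babies with encephalopathy, without assigning them to the disease. Bring the sentence on the expected window into line with a list that includes later outcomes.
3. State that all deaths and serious events up to final follow-up, listed or not, are tabulated by masked arm for the existing IDMC reviews and by arm in the final report, regardless of attributed cause.

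The review schedule need not change, and the 24 h route for serious unlisted events can stay as it is. The cost is a wording change and slightly more tabulation, from data largely collected already: the case report form reaches the trial manager within 48 h of death or discharge, and infancy morbidities are recorded at follow-up.

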The sample size is based on being able to detect a clinically significant 30% relative risk reduction in death or moderate/severe disability from 50% in the usual care arm to 35% in the intervention (cooled) arm. Using a two-sided 5% significance level and an 80% power, 183 babies per arm are required. Assuming a loss to follow-up rate of around 10%, this comparison requires 204 babies per group, 408 babies in total, to be recruited. In case the adverse outcomes (death and moderate/severe disability) are higher (~65%) in the usual care arm, then this sample size would provide 94% power to detect a 30% relative risk reduction with cooling.

Each CRF (pdf) will be send to the HELIX trial manager within 48 h of discharge/death and all data queries will be resolved in real time by the HELIX research nurse/data entry person. The CRF will be signed off for completion and entered into the HELIX Redcap database by a dedicated data entry person at Imperial College London. The HELIX trial manager will then forward the trial data to an independent statistician, after masking the allocation (as X and Y) for analysis. The trial statistician will analyse the data for IDMC meetings as per a predefined proforma (masked as A and B), at six-monthly intervals or after recruitment of every 50 cases whichever is earlier. The temperature data will be reported to the IDMC as adherence to target temperature, rather than actual temperatures to prevent unmasking of the IDMC members. The principal investigators will not have access to the trial data before locking, nor will they have any role in the data analysis. The trial CONSORT diagram is given in Fig. 2.

**Fig. 2 Fig2:**
[figure not shown]
CONSORT *diagram*

## Trial organisation

### Independent Data Monitoring Committee (IDMC)

An IDMC will review the study’s progress. The IDMC will be independent of the trial organisers. The IDMC will meet every six months or after recruitment of 50 babies, whichever is earlier.

Meetings of the committee will be arranged periodically, as considered appropriate by the Chair.

The IDMC will inform the Trial Steering Committee (TSC) if in their view:there is proof beyond reasonable doubt that the data indicate that any part of the protocol under investigation is either clearly indicated or contra-indicated, either for all infants or for a subgroup of trial participants;it is evident that no clear outcome will be obtained;safety signal.

The primary endpoint will be assessed 18 months after the intervention has been performed. Given the planned period of recruitment, the primary endpoint will not be able to be assessed until majority of patients have been recruited. Thus, it will not be possible to stop the study early based on the study outcomes.

The membership of IDMC is detailed below:[name] (Chair, Professor for Neonatology, Brown University, USA)[name] (Faculty of Epidemiology and Population Health, London School of Hygiene and Tropical Medicine, London, UK)[name] (Professor of Neonatology, Christian Medical College, Vellore, India)[name] (Consultant Neonatologist, Medway Hospital NHS Trust, Kent, UK)

The HELIX trial statistician will provide the trial data for IDMC meetings according to a pre-defined reporting format agreed by the IDMC.

### Trial Steering Committee

The TSC will provide overall supervision of the study of the Sponsor. Its terms of reference are:to monitor and supervise the progress of the HELIX trial towards its interim and overall objectives;to review at regular intervals relevant information from other sources (e.g. related studies);to consider the recommendations of the IDMC.

### Project Management Group

The Project Management Group will oversee all aspects of the day-to-day running of the study and will consist of the investigators and the HELIX trial staff, based at the HELIX Co-ordinating Centre at Madras Medical College, Chennai, India and the Centre for Perinatal Neuroscience, Imperial College London. The Project Management Group will hold a monthly teleconference of all HELIX investigators for the entire duration of the trial to discuss the data quality and recruitment.

All correspondence with the REC will be retained in the Trial Master File/Investigator Site File. Annual reports will be submitted to the REC in accordance with Imperial College London requirements. It is the Chief Investigator’s responsibility to produce the annual reports as required. Each participating site in India will have local research ethics and other regulatory approvals as per the local regulations.

